## **6.6 Index test and reference standard test procedures**

Test procedures for the reference tests and the RDT index tests will be performed according to the manufacturer's IFU, which are provided separately from this protocol.

### **6.6.1 Index tests procedure summary**

Wantai RDT: one drop of whole blood or 50 µl of serum/plasma, 1 drop of buffer, 10 min incubation time

PMC RDT: one drop of whole blood or 35 µl of serum/plasma, 1 drop of buffer, 20 min incubation time

AccessBio: 10 µl of whole blood, serum or plasma, 2 drops of buffer, 15 min incubation time  
RDT

The fingerstick whole blood sample will be applied with a small pipette provided with the kit and according to the manufacturer's instructions. Plasma and serum samples will also be applied with a small pipette, which the manufacturers will provide additionally, as each test only includes one pipette. All RDTs contain a procedural/sample control line to check and verify that sample has been applied and the procedure was performed correctly.

### **6.6.2 Reference tests for composite reference standard**

- EIA 1: Diasorin Murex Anti-HCV 4.0
- EIA 2: Fujirebio INNOTEST HCV Ab IV
- LIA: Fujirebio INNO-LIA HCV Score

The composite reference standard is designed of two EIAs and one LIA.

While EIAs have overall good performance characteristics [21, 22], the LIA is intended to serve as a more specific supplemental tests in samples reactive by EIA [23]. In addition to high specificity, the LIA has very good sensitivity. Both performance characteristics are owed to the presence of individual recombinant antigen lines on the LIA membrane.

Due to the intended superior performance characteristics of LIA to EIAs, any samples which have discrepant results in the EIAs to the LIA will be excluded from the main analysis of the study (i.e. 2x positive EIA and negative LIA or 2x negative EIA and positive LIA) to minimize the risk of false-negatives or false-positives results from the composite reference standard. In case of a discrepant results in the EIA, the LIA is the decision-making test result (see also Table 8).

This algorithm is used by WHO PQ for sample characterisation during the independent laboratory evaluations of RDTs [17], with the exception that LIA is not performed on samples which are negative with both EIAs. For the present study, it was decided that all samples will be tested by LIA, like in the previous evaluation of HCV RDT led by FIND [4]. In this study, a small subset of samples negative in both EIAs was positive or indeterminate in LIA, suggesting the presence of HCV antibodies.

Further combinations of the reference results will be used to assess tests performance in borderline and more difficult samples (for further details see section 8.4.1).

### **6.6.3 Discordant results**

Discordant results of the study RDTs to the WHO PQed RDT (SD Bioline) will be repeated for EDTA plasma and serum samples only, as the participant may not be available for repeat testing of fingerstick whole blood. Discordant results will be repeated in duplicate within 24h at the primary healthcare facility, using the same lot.

Performance analysis will be conducted using initial results only. The results of further testing of samples with discrepant results will be reported separately as additional information about RDT performance.

### **6.6.4 Training**

All healthcare workers at the enrolment sites will be trained in the procedures of the study RDTs, including workflow of test reading and result recording. Training will be performed on known positive and negative plasma or serum samples, as well as on fingerstick whole blood. Interpretation of RDT bands will be trained on pre-conceived RDTs provided by the manufacturers or obtained by serial dilutions of known positive samples. Proficiency will be documented in a training log.

Training on the reference tests will be restricted to reviewing the IFU as the chosen laboratories are familiar with the performance of EIAs and LIA. Prior to starting sample testing on EIA, a positive IRC needs to be adjusted to fall within the low cut-off range of the specific EIAs. This adjustment testing can serve as training runs in case the laboratory technicians are not familiar with the exact procedure of the study-specific EIAs. Familiarization of the test procedures will be documented in a training log.

## **6.7 Confirmatory testing and genotyping**

All participants with an initially reactive RDT will have an HCV viral load assessment and the HCV genotype assessed in case of sufficiently high viral load (depending on the genotyping kit's IFU on minimum needed RNA). See section 4.1 for specific products. No genetic analysis will be performed on human genetic material.

## **6.8 Experimental Biomarkers**

Left-over samples may be used for research to develop or evaluate methods, assays, prognostics and/or companion diagnostics related to other infectious viral hepatitis diseases or potentially frequently found co-infections in affected target populations (such as HIV or TB).

Samples will be stored for a maximum of 5 years at the ZeptoMetrix biorepository (or until FIND agrees that samples can be destroyed), following the last participant's sample collection for the study. The participants will be asked to provide a separate informed consent for further sample analysis (see also section 9.3 Informed consent process).

## 6.9 Other tests

Every study participant will receive an HIV test, as HIV infection may influence HCV RDT test performance due to lower antibody titres in immunocompromised patients [19, 20]. This may allow to draw conclusions on false negative RDT results.

Reactive HIV RDT results will be followed up with the standard of care confirmatory test. The results will be communicated to the participant through the participant's physician. All enrolled participants have consented to the performance of an HIV test, which will be performed if a positive HIV status is not documented in their medical record or the last negative HIV test result is older than 12 months.

## 6.10 Safety assessments

There will be no planned safety assessments as the risks for the participants are considered minimal (see section 1.3).

## 6.11 Other study procedures

A technical appraisal of each RDT product per manufacturer will be completed at the end of the study jointly by all healthcare workers who have performed this test. The appraisal will be documented in the "RDT Technical Appraisal Form" (see Appendix 3). Each site completes one technical appraisal form per manufacturer.

# 7 Safety and incident reporting

Given that this is a diagnostic accuracy study of HCV RDT assays, the probability of an adverse event (AE) or a serious adverse event (SAE) occurring to a study participant to be associated with the investigational products is extremely low (see Appendix 1 for definitions of AE or SAE). Considering this, only deaths occurring between the start of the fingerstick blood collection and until the participant leaves the study will be recorded on a standardized form and reported to FIND by the investigator within 24 hours.

## 7.1 Medical device incidents (including malfunctions)

Medical devices are being provided for use in this study for the purpose of evaluating HCV RDT diagnostic accuracy. In order to fulfil regulatory reporting obligations worldwide, the investigator is responsible for the detection and documentation of events meeting the definitions of incident or malfunction that occur during the study with such devices. The definition of a medical device incident can be found in Appendix 2.

Examples of a medical device incident for this study could be:

- A broken safety lancet provided in the RDT kit (if provided)
- A broken or malfunctioning capillary tube or pipette provided in the RDT kit

NOTE: Incidents fulfilling the definition of an SAE will also follow the processes outlined above and in Appendix 2 of the protocol.

### **7.1.1 Time period for detecting medical device incidents**

Medical device incidents or malfunctions of the device that result in an incident will be detected, documented, and reported during all periods of the study in which the medical device is used.

If the investigator learns of any incident at any time after a participant has been discharged from the study, and such incident is considered reasonably related to a medical device provided for the study, the investigator will promptly notify FIND.

The method of documenting medical device incidents is provided in Appendix 2.

### **7.1.2 Follow-up of medical device incidents**

All medical device incidents involving a SAE will be followed up and reported in the same manner as other SAEs. This applies to all participants, including those who discontinue study intervention.

The investigator is responsible for ensuring that follow-up includes any supplemental investigations as indicated to elucidate the nature and/or causality of the incident.

New or updated information will be recorded on the originally completed form with all changes signed and dated by the investigator.

### **7.1.3 Reporting of medical device incidents to FIND**

Medical device incidents will be reported to FIND within 24 hours after the investigator determines that the event meets the protocol definition of a medical device incident.

The Medical Device Incident Report Form will be sent to FIND by email. If email is not available, a mobile phone picture can be taken and sent via messaging service.

The same individual(s) will be the contact for the receipt of medical device incident reports and SAE reports.

### **7.1.4 Regulatory reporting requirements for medical device incidents**

The investigator will promptly report all incidents occurring with any medical device provided for use in the study in order for FIND to fulfil the legal responsibility to notify appropriate regulatory authorities and other entities about certain safety information relating to medical devices being used in clinical studies.

The investigator, or responsible person according to local requirements (e.g., the head of the medical institution), will comply with the applicable local regulatory requirements relating to the reporting of incidents to the IRB/IEC.

## 8 Statistical considerations

### 8.1 Statistical hypotheses

No statistical hypotheses will be tested in this study.

### 8.2 Sample size determination

For the three RDTs – Wantai, PMC and AccessBio – the previous FIND HCV RDT study [4] estimated an overall sensitivity of 97.1%, 95.9% and 96.1%, and an overall specificity of 97.5%, 99.5% and 97.8% in EDTA plasma, respectively (unpublished data).

Considering the possibility of a lower performance in fingerstick whole blood in primary healthcare settings, the sensitivity and specificity for these RDTs in the present study was conservatively assumed to be 90%. For fresh EDTA plasma and serum, sensitivity and specificity were assumed to be similar to the previous study, i.e. at least 95%.

Considering that the study aim is to obtain point estimates of sensitivity and specificity and positive and negative predictive values for each test, the assumed values of 90% performance in whole blood and 95% performance in EDTA plasma/serum were used as reference to calculate the sample size so that the study would have 80% power to obtain the estimates with a precision of  $\pm 5\%$ . The minimum sample size required was determined following the methods described in “Statistical Methods in Diagnostic Medicine”, chapter 6 [24].

The study sample was increased from the statistically required minimum in order to meet the requirements in the WHO Technical Specification Series document “TSS-7: Rapid diagnostic tests to detect hepatitis C antibody or antigen” (still in draft) [6]. The WHO TSS-7 requires at least 400 HCV antibody positive samples to be evaluated for sensitivity in fresh whole blood, and at least 1'000 HCV antibody and HCV RNA negative samples for specificity in fresh whole blood. An additional 10% was added to the required sample size to account for sample exclusion due to non-confirmed antibody status based on the composite reference standard (see **Error! Reference source not found.**). This number was based on experience from the previous FIND HCV RDT study, which used the same composite reference standard [4].

**Table 4** reports the minimum sample size requirements calculated and the final sample size for this study.

**Table 4:** Sample size

|                         |             | Estimated performance | Power | Margin | Statistical sample size requirement | WHO TSS-7 sample size requirement | Final sample size for this study |
|-------------------------|-------------|-----------------------|-------|--------|-------------------------------------|-----------------------------------|----------------------------------|
| Fingerstick whole blood | Sensitivity | 90%                   | 0.8   | 0.05   | 283                                 | 400                               | 440                       |
|                         | Specificity | 90%                   | 0.8   | 0.05   | 283                                 | 1'000                             | 1'100                     |
| EDTA plasma             | Sensitivity | 95%                   | 0.8   | 0.05   | 150                                 | 400                               | 440                       |
|                         | Specificity | 95%                   | 0.8   | 0.05   | 150                                 | 1'000                             | 1'100                     |
| Serum                   | Sensitivity | 95%                   | 0.8   | 0.05   | 150                                 | 400                               | 440                       |
|                         | Specificity | 95%                   | 0.8   | 0.05   | 150                                 | 1'000                             | 1'100                     |

Each participant will provide samples for all sample types (see also Figure 2), resulting in a total of 1'540 matched fingerstick whole blood, EDTA plasma and serum sample sets.

Enrolment targets per country and site are listed in **Table 5**. Targets take into consideration local HCV prevalence and estimated number of patients to be enrolled per day

**Table 5** Enrolment targets per country and site

|                             | Approximate HCV prevalence           | Estimated number of patients recruited per day | HCV antibody positive participants | HCV antibody/RNA negative participants | Total                    |                 |
|-----------------------------|--------------------------------------|------------------------------------------------|------------------------------------|----------------------------------------|--------------------------|-----------------|
| Georgia OST site            | 40% + patients with known HCV status | 25                                             | 310                                | 140                                    | 450 per site             | 770 per country |
| Georgia NCDC screening site | 5%                                   | 15                                             | 20                                 | 300                                    | 320 per site             |                 |
| SHCH outpatient site        | 5% + patients with known HCV status  | 25                                             | 110                                | 660                                    | 770 per site and country |                 |

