| Sample Size          | 
In the previous FIND HCV RDT study, the average performance of sensitivity and specificity in EDTA plasma of the three selected tests was 96.3% and 98.3%, respectively. Based on this, a conservative assumption on performance in fresh samples in the hands of the intended user was made, setting the expected average sensitivity and specificity to 90% in whole blood and 95% in EDTA plasma and serum.
 
To obtain a reliable performance estimate, the following sample sizes were determined:
 
Sensitivity:
 
 
• 440 whole blood HCV antibody positive
 
• 440 EDTA plasma HCV antibody positive
 
• 440 serum HCV antibody positive
 
 
note: a total of 440 participants will be enrolled and each participant will provide whole blood, EDTA plasma and serum samples
 
Specificity:
 
 
• 1'100 whole blood HCV antibody and HCV RNA negative
 
• 1'100 EDTA plasma HCV antibody and HCV RNA negative
 
• 1'100 serum HCV antibody and HCV RNA negative
 
 
Note: a total of 1'100 participants will be enrolled and each participant will provide whole blood, EDTA plasma and serum samples
 
These sample sizes meet the requirements of the WHO Technical Specification Series document TSS-7: "Rapid diagnostic tests to detect hepatitis C antibody or antigen" (still in draft) for evaluation of clinical sensitivity and specificity.
 
Each primary healthcare facility will have set enrolment targets to avoid unbalanced recruitment.
 |

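### Adding 10% to the TSS-7 minima (440 and 1,100) leaves 396 and 990 if 10% of samples are then excluded, just under the 400 and 1,000 the plan says it meets

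*Protocol*

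**What the plan says.** Section 8.2 of the protocol quotes the draft TSS-7 requirement as a lower bound for each group. For positives: "The WHO TSS-7 requires at least 400 HCV antibody positive samples to be evaluated for sensitivity in fresh whole blood". For negatives: "at least 1'000 HCV antibody and HCV RNA negative samples for specificity in fresh whole blood". On top of these it makes one allowance: "An additional 10% was added to the required sample size to account for sample exclusion due to non-confirmed antibody status". The source of the allowance is given as follows: "This number was based on experience from the previous FIND HCV RDT study, which used the same composite reference standard".

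Table 4 carries the result, 440 for sensitivity and 1,100 for specificity, in whole blood, EDTA plasma and serum alike. The synopsis lists the same figures ("440 whole blood HCV antibody positive" and "1'100 whole blood HCV antibody and HCV RNA negative"), notes that these are numbers of participants to be enrolled, and concludes: "These sample sizes meet the requirements of the WHO Technical Specification Series document TSS-7".

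Sections 6.6.2 and 8.4.1 (Table 8) define the exclusions. Samples on which both EIAs contradict the LIA, and samples with an indeterminate LIA, leave the main analysis. Section 8.4.1 evaluates outcomes 1.1 and 2.1 on the per-protocol population, which Table 6 limits to participants with index and reference results for all tests.

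**The concern.** A loss allowance should be sized so that the required number remains after the loss. Multiplying by 1.10 does not do this for a 10% loss, because the loss is taken from the enlarged number: 1.10 × 0.90 = 0.99. The evaluable sample then ends 1% below the requirement.

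In most trials a 1% gap would not deserve comment. Here the requirement is a stated minimum, and section 8.2 gives meeting it as the reason for raising the sample above the statistical minimum of 283 (whole blood) or 150 (plasma and serum). What is at stake is whether the plan's statement that it meets TSS-7 holds for the samples that will actually be analysed.

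**Working it through.** **Inputs**
- Minima: 400 positives, 1,000 negatives (section 8.2, Table 4).
- Allowance: 10% (section 8.2).
- Enrolled targets: 440 and 1,100, total 1,540 (synopsis, Tables 4 and 5).
- Assumed here: the 10% is the expected exclusion rate, and it applies equally to both groups. The protocol states neither outright.

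**Reproducing the plan's figures**
- n × (1 + 0.10): 400 × 1.10 = 440 and 1,000 × 1.10 = 1,100. Both match exactly.
- Table 5: 310 + 20 + 110 = 440 and 140 + 300 + 660 = 1,100. The site targets hold no hidden reserve.
- Statistical minimum, (1.96 + 0.8416)² × p(1 − p)/0.05², taking a two-sided 5% level: 282.6, rounded up to 283, at p = 0.90; 149.1, rounded up to 150, at p = 0.95. Both match Table 4.

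**What remains after a 10% exclusion**
- 440 × 0.90 = 396, which is 4 below 400.
- 1,100 × 0.90 = 990, which is 10 below 1,000.

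**Largest tolerable exclusion**
- 1 − 400/440 = 1 − 1,000/1,100 = 9.09% in each group, with no loss for any other reason.

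**Chance of keeping each minimum with 440 and 1,100** (binomial, independent exclusions)

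| True exclusion rate | At least 400 of 440 | At least 1,000 of 1,100 |
|---|---|---|
| 10% | 29% | 17% |
| 9% | 57% | 57% |
| 8% | 83% | 92% |
| 5% | over 99.9% | over 99.9% |

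**Targets sized for a 10% loss**
- n/(1 − 0.10): 400/0.90 = 444.4, rounded up to 445; 1,000/0.90 = 1,111.1, rounded up to 1,112. The total is 1,557 against 1,540, so 5 more positives and 12 more negatives.
- Expected to remain: 445 × 0.90 = 400.5 and 1,112 × 0.90 = 1,000.8. These meet the minima only on average. At a true rate of 10% the chance of reaching each one is about 57% and 56%.

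**Effect on precision** (95% half-width 1.96 × √(0.09/n), at 90% performance)
- Positives: 2.95 points with 396, 2.94 with 400.
- Negatives: 1.87 points with 990, 1.86 with 1,000.

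**The case against.** The strongest reply is that the protocol never states a 10% exclusion rate. It adds 10% on the strength of experience in an earlier study whose figures are not given. If the true rate is 9.09% or less, nothing is missed. This stands, and it is why the point is conditional. Still, an allowance of 10% made for exclusions, and said to rest on past exclusions, is most naturally read as the rate expected.

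It can also be said that the synopsis claim is literally true of the planned sizes, since 440 exceeds 400 and 1,100 exceeds 1,000. That is so for enrolled participants. But the requirement concerns samples evaluated, and the allowance exists because some enrolled samples will not be. Reading 440 and 1,100 as counts after reference confirmation would remove the shortfall, but it would leave the 10% without a purpose and would not fit the synopsis note that these are enrolment numbers.

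The gap is about 1%, and TSS-7 is still a draft. Both are true, and they limit the weight of the point.

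Three stronger readings are tempting and are not supported:
- **That the shortfall undermines a WHO submission.** The protocol does not say what follows from missing a minimum by 1%.
- **That the 20 positives planned for the "Georgia NCDC screening site" cannot be reached, which would deepen the gap.** At exactly 5%, 320 enrolments give 16 positives. But Table 5 calls the prevalence approximate, 20 of 320 needs only 6.25%, and section 1.2 puts national seroprevalence at 7.7% (about 25 of 320). The other two sites also contact known positives and could absorb four.
- **That missing or invalid RDT results add a definite further loss.** Invalid runs are repeated at once (sections 3.1.1 and 6.2.1), and no rate of missing results is given. All that can be said is that the plan leaves no margin for such losses.

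**Conclusion.** The point holds in a limited form. The allowance is multiplicative, so a 10% exclusion by the composite reference standard would leave an expected 396 positives and 990 negatives, 4 and 10 short of the minima that the synopsis says are met. The conclusion rests on three assumptions: that 10% is the expected exclusion rate, that it applies equally to both groups, and that 440 and 1,100 are counts before exclusion. Only the third has direct support, in the synopsis. At 9.09% or less, with no other loss from the per-protocol population, there is no shortfall.

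This is a matter of consistency with a stated minimum, not of statistical adequacy: both counts stay far above 283, and the confidence intervals are practically unchanged. Section 8.2 ties the minima to fresh whole blood; only Table 4 extends them to plasma and serum, so the finding is firmest for whole blood.

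**What to change.** State the assumed exclusion rate in section 8.2, then correct Table 4 and the synopsis claim in one of two ways:

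1. **Restate the targets** as 445 positives and 1,112 negatives (total 1,557), adjust Table 5 to match, and note that these meet each minimum only on average at 10% exclusion. The cost is 17 more participants.
2. **Keep 440 and 1,100**, state that they leave 396 and 990 at 10% exclusion and tolerate at most 9.1%, and qualify the statement that TSS-7 is met. The cost is wording only.

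Optionally, define the Table 5 targets as reference-confirmed, evaluable counts, and close each group when its minimum is reached. This protects the minima best and needs no guess at the rate. Reference testing is planned within 7 days, so it looks feasible, but reference results (running counts would do) must be fed back to the sites during recruitment, and the number enrolled is then not fixed in advance.
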